## Abstract

There is an increasing burden of neurodevelopmental disorders worldwide, with scarce data in low and middle-income countries, including Nigeria. Little is known about Fragile X disorders (Fragile X syndrome and Fragile X premutation-associated conditions) in developing countries and there is no national data in Nigeria. Advancing Mental Health and Well-being of Nigerian Children Through Public Health Screening for Fragile X Disorders (CHAMP-FX) is a multicentre public health screening initiative designed to estimate the prevalence of Fragile X disorders among children with neurodevelopmental disorders in Nigeria through targeted screening, strengthen diagnostic capacity and provide pathways to targeted treatments. This is a prospective multicentre screening study with longitudinal follow-up recruiting children aged 1–18 years with intellectual disability, autism spectrum disorder, and/or global developmental delay from six tertiary hospitals across Nigeria’s six geopolitical zones. Using purposive sampling, 102 participants (17 per zone) will be enrolled. Sociodemographic data and clinical evaluation will be obtained using KoboToolbox. Blood samples will be collected as dried spots on quick-response coded filter cards, stored with desiccant, and transported to the coordinating molecular laboratory. Genetic testing will be performed using a long-range amplification workflow followed by long-read sequencing to determine repeat sizes and classify results using internationally accepted thresholds. The primary outcome is the proportion of participants with Fragile X full mutation and/or premutation in the selected cohort. Secondary outcomes include the distribution of repeat sizes and associations with sociodemographic and clinical variables. Screen-positive participants will receive structured result disclosure, genetic counselling, and referral for appropriate supportive interventions, with targeted therapy using metformin offered to participants diagnosed with Fragile X syndrome. Findings will be disseminated through peer-reviewed publication, conferences and stakeholder engagement.

## Introduction

Neurodevelopmental disorders such as intellectual disability, global developmental delay, and autism significantly contribute to lifelong disability and mental health challenges globally [1].

Fragile X syndrome (FXS) is the leading inherited cause of intellectual disability and a major single-gene contributor to autism, resulting from cytosine-guanine-guanine (CGG) trinucleotide repeat expansion (>200 repeats) in the 5′ untranslated region (5’UTR) of the fragile X mental retardation 1 (*FMR1)* gene, resulting in gene silencing and reduced/absent fragile X mental retardation protein (FMRP) and subsequent synaptic dysfunction [2–4].

Beyond full mutation FXS, individuals carrying *FMR1* premutation alleles (approximately 55–200 CGG repeats) are at risk of Fragile X–associated premutation conditions, including Fragile X–associated primary ovarian insufficiency (FXPOI), Fragile X–associated tremor/ataxia syndrome (FXTAS), and Fragile X–associated neuropsychiatric disorders (FXAND), thereby extending the clinical and psychosocial burden of *FMR1*-related disorders also known as Fragile X disorders across the lifespan [4,5].

There have been significant global advances in diagnosis and targeted supports, in Nigeria, Fragile X disorders are rarely identified in routine clinical practice, mainly due to low awareness, limited access to molecular diagnostics, and persistent sociocultural stigma surrounding neurodevelopmental conditions [1,5–7] This implies that affected children and families experience delays in management, while policymakers and clinicians lack the data required for informed service planning.

The World Health Organisation has emphasised early identification and intervention for developmental challenges in low and middle-income countries (LMICs) and highlighted neglected needs of children with developmental disabilities [8]. CHAMP-FX aligns with these priorities and conducts a multi-site screening approach in high-risk paediatric populations, thereby strengthening local capacity for Fragile X testing and follow-up.

## Objectives

Overall aim: To advance Nigerian children’s mental health and well-being through a public health screening initiative for Fragile X disorders (CHAMP-FX).

### Specific objectives

To estimate the prevalence of Fragile X full mutation and premutation among Nigerian children (1–18 years) with intellectual disability, autism spectrum disorder, or global developmental delay using molecular methods.To identify sociodemographic and clinical factors associated with Fragile X disorders in this population.To establish screening-to-care pathways, including result disclosure, genetic counselling, and referral for supportive interventions.To develop a context-appropriate model for integrating Fragile X screening into paediatric/developmental health services in Nigeria.

## Materials and methods

### Study Setting and Study design

Nigeria is a country in West Africa with an estimated 2024 total population of 232,679,478 [9]. The country comprises six geopolitical zones (North-central, north-east, north-west, south-east, south-south and south-west), each with distinct sociocultural and healthcare characteristics. CHAMP-FX is a prospective multicentre screening study with longitudinal follow-up to be conducted across six tertiary hospitals representing Nigeria’s six geopolitical zones. This approach enables the study to track outcomes over time, assess longitudinal screening outcomes, referral processes, and implementation feasibility.

The coordinating centre is Nnamdi Azikiwe University/Teaching Hospital, Nnewi, Anambra State, south-east Nigeria. The study sites will include Nnamdi Azikiwe University/Teaching Hospital, Anambra (Coordinating centre)- (Southeast), Benue State University Teaching Hospital, Benue (Northcentral), Federal Medical Centre, Asaba, Delta (Southsouth), Aminu Kano Teaching Hospital, Kano (Northwest), Federal Teaching Hospital, Gombe (Northeast), and Federal Medical Centre, Ebute-Metta, Lagos (Southwest).

### Study population

Children aged 1–18 years attending paediatric neurology/paediatric clinics with a diagnosis of: intellectual disability, autism spectrum disorder, and/or global developmental delay. Autism spectrum disorder, intellectual disability and global developmental delay were confirmed using the DSM-5 diagnostic criteria through multidisciplinary assessments conducted by a trained neurodevelopmental paediatrician, paediatric neurologists and a psychologist. Autism spectrum disorder was diagnosed based on developmental history, clinical observation and behavioural assessment. For children younger than 4 years, the Ages and Stages Questionnaire, Third Edition (ASQ-3), was used to assess developmental delay. For children aged 4 years and older, the Raven’s Standard Progressive Matrices (Revised 2019) was used to assess intellectual functioning as part of the evaluation for intellectual disability.

### Study period

The study is scheduled to run from October 2025 to September 2027, following fund disbursement. Participant recruitment is planned between February and September 2026. Data collection is expected to be completed by January 2027, with analysis and results anticipated by May 2027. Follow-up will be conducted across the six sites. These timelines are projected estimates and may be adjusted in response to operational, logistical, or field conditions. (S1 Table)

### Eligibility criteria

Inclusion: Age 1–18 years, clinical diagnosis of intellectual disability, autism spectrum disorder, or global developmental delay; and parent/guardian provides written informed consent (and child assent where appropriate). Children whose parent/guardian declines consent will be excluded. See Appendix A

### Sample size and allocation

The minimum sample size was calculated using the formula [10]: Z2Pq/d2 n = unadjusted minimum sample size, Z = 1.96, P = 0.023 [11], q = 1-P = 0.977, d = standard error (5%, 0.05). Therefore, $n=\frac{\text{1}.\text{96 x }\text{1}.\text{96 x }\text{0}.\text{023 x }\text{0}.\text{977}}{\text{0}.\text{05 x }\text{0}.\text{05}}$ = 34.5. To adjust for a finite population, the formula $nc=\frac{\text{n}}{\text{1}+(\frac{\text{n}}{\text{N}})}\;$will be used, where nc is adjusted minimum sample size, N = Population from the record (from the records, 12 cases of autism are seen every 5 months in NAUTH, Nnewi, Anambra State. This amounts to 28.9 patients every year). $nc=\frac{\text{34}.\text{5}}{\text{1}+(\frac{\text{34}.\text{5}}{\text{28}.\text{9}})}$ = 15.7 (minimum sample size). For the purpose of this study, 17 participants will be selected per geo-political zone, yielding 102 study participants. Due to the absence of national prevalence data on Fragile X syndrome among high-risk children in Nigeria, the sample size was estimated using patient records from the coordinating centre, a major referral centre for neurodevelopmental disorders. These represented the best available local data to inform the study design. While this may not fully capture regional variation, the multicentre design will enhance the representativeness of the study findings.

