### Sampling technique

Purposive sampling of eligible clinic attendees will be used at each site until the zone allocation is achieved. To ensure national representation and account for regional variability: Equal allocation of participants was adopted, with 17 children per zone, resulting in a total of 102 participants. This pragmatic sample is intended to estimate prevalence estimates within this high-risk clinical cohort and support exploratory analyses of correlates.

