### Outcomes

The primary outcome is the proportion of participants with *FMR1* full mutation and/or premutation (those who test positive from the screening) in the selected cohort. Secondary outcomes include the distribution of CGG repeat sizes; the association of FMR1 expansion status with sociodemographic and clinical variables; the proportion of screen-positive families receiving counselling, referrals, and linkage to supportive interventions relevant to child mental health and developmental wellbeing; uptake of cascade testing offers; and building research capacity through mentoring early-career faculty members towards training in public health genetics. The study findings will be reported in accordance with the Strengthening the Reporting of Observational Studies in Epidemiology (STROBE) Statement.

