### Statistical analysis plan

Data will be analysed using STATA version 16 (StataCorp LLC, College Station, TX, USA). Descriptive statistics will be performed using means/Standard deviation or medians/Inter-quartile range for continuous variables. Frequencies/percentages will be calculated for categorical variables. Prevalence estimates will be at 95% confidence intervals while Chi-square or Fisher’s exact tests used for categorical variables where appropriate to test for associations. Logistic regression analyses will be performed to identify factors associated with Fragile X positivity if the number of positive cases is sufficient to support reliable multivariable modelling. Where the number of positive cases is insufficient, analyses will be limited to descriptive and bivariate methods.

Statistical significance will be set at p < 0.05.

We will minimise potential sources of bias through recruitment across Nigeria’s six geopolitical zones, standardised eligibility criteria and data collection procedures, centralised laboratory analysis using validated protocols, and prespecified statistical analyses.

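### The sample size rests on a 5-point margin, mislabelled a standard error, around an assumed prevalence of 2.3%, so it does not justify 102 children for the primary proportion

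*Protocol article*

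**What the plan says.** All references are to the protocol article.

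- **Sample size and allocation.** "The minimum sample size was calculated using the formula [10]: Z2Pq/d2", with Z = 1.96, "P = 0.023 [11], q = 1-P = 0.977" and "d = standard error (5%, 0.05". This gives 34.5. A finite-population adjustment, with N taken from one centre's records ("This amounts to 28.9 patients every year"), lowers it to 15.7. The section then sets the recruitment: "17 participants will be selected per geo-political zone, yielding 102 study participants".
- **Sampling technique.** "This pragmatic sample is intended to estimate prevalence estimates within this high-risk clinical cohort and support exploratory analyses of correlates".
- **Outcomes.** The primary outcome is a single proportion in the whole cohort, counting full mutation and/or premutation.
- **Statistical analysis plan.** "Prevalence estimates will be at 95% confidence intervals". No interval method is named.

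No section gives an expected interval width or an expected number of positives for the pooled 102.

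**The concern.** Two things in the sample size paragraph do not fit together. The quantity called a standard error is used as a margin of error. That margin, 5 percentage points, is larger than the prevalence it is meant to bracket. A target of 2.3% plus or minus 5 points has an impossible lower limit and cannot separate the assumed value from zero. The formula is also a normal approximation, applied where fewer than one positive child is expected.

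At stake is how the primary result is read. It will probably rest on very few positives, and none at all is a realistic result. The protocol intends its findings to inform policy, service planning and a screening integration model. A reader who trusts the stated calculation has no warning of how wide the interval will be, or of what an empty result would mean.

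**Working it through.** **Inputs, all from the sample size section:** Z = 1.96, P = 0.023, q = 0.977, d = 0.05, N = 28.9, and 17 × 6 = 102.

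**1. Reproduce the plan's figures.**
n = Z²Pq/d² = 1.96² × 0.023 × 0.977 / 0.05² = 34.53 (stated 34.5).
nc = 34.5 / (1 + 34.5/28.9) = 15.73 (stated 15.7).
Both reproduce. Twelve cases per 5 months annualises to 28.8 rather than 28.9, which leaves nc at 15.7.

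**2. What is d?**
If 0.05 were a standard error, n = Pq/d² = 0.022471 / 0.0025 = 9.0. The stated 34.5 arises only if d is the 95% half-width.

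**3. The target interval.**
0.023 ± 0.05 = -2.7% to 7.3%. Ratio of margin to prevalence: 0.05 / 0.023 = 2.2.

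**4. The normal approximation at the planned minimum.**
Expected positives = 34.5 × 0.023 = 0.79. Chance of none = 0.977^34.5 = 45%.

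**5. What 102 gives if P = 0.023.**
- Half-width by the plan's own formula: 1.96 × √(0.022471/102) = 2.9 points, so -0.6% to 5.2%.
- Expected positives: 102 × 0.023 = 2.35.
- Chance of none: 0.977^102 = 9.3%. Chance of one: 22.4%. Chance of at most one: 31.7%.

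**6. Intervals at n = 102, by number of positives.**

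| Positives | Exact (Clopper-Pearson) 95% | Wilson 95% | Wald 95% |
|---|---|---|---|
| 0 | 0 to 3.6% | 0 to 3.6% | zero width |
| 1 | 0.02% to 5.3% | 0.2% to 5.4% | -0.9% to 2.9% |
| 2 | 0.2% to 6.9% | 0.5% to 6.9% | -0.7% to 4.7% |
| 3 | 0.6% to 8.4% | 1.0% to 8.3% | -0.3% to 6.2% |

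The exact upper limit for 0/102 is 1 - 0.025^(1/102) = 3.6%. Wald limits are x/102 ± 1.96 × √[(x/102)(1 - x/102)/102]. At P = 0.023 the four rows together have probability 9.3% + 22.4% + 26.6% + 20.9% = 79%. By enumeration over the binomial distribution, the Wald interval covers the true value 90.4% of the time at n = 102 and P = 0.023; the exact interval covers it 99.1%.

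**7. Sensitivity to P.** The other values are assumptions, for illustration.

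| True proportion | Expected positives in 102 | Chance of none |
|---|---|---|
| 1% | 1.0 | 36% |
| 2.3% | 2.3 | 9.3% |
| 3% | 3.1 | 4.5% |
| 5% | 5.1 | 0.5% |

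**The case against.** The case on the other side has real force on several points.

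- **A reader might infer that a Wald interval is planned.** The protocol does not say so. A planning formula does not fix the analysis interval, and the choice may well be made in a document not shown here. The same section allows for sparse data: Fisher's exact test where appropriate, and regression only if there are enough positives. The unnamed method is therefore no defect in itself. The Wald figures show only why that choice should be avoided.
- **A reader might infer that the study's precision is meaningless.** That goes too far. The 5-point margin belongs to the unadjusted minimum of 34.5. With 102 enrolled, the same formula gives about 2.9 points, and an exact interval has a valid lower limit and an informative upper one.
- **A reader might apply the calculation to 17 children per zone.** The primary outcome is one pooled proportion, so 17 is not its unit of analysis.
- **A reader might call this an arithmetic error.** It is not: 34.5 and 15.7 both reproduce. The fault is a wrong label and an ill-chosen margin.
- **The value 2.3% may not apply to the primary outcome.** The sample size section refers to Fragile X syndrome, whereas the primary outcome also counts premutations. A higher proportion would make an empty result much less likely.
- **The protocol is modest about its aims.** It calls the sample pragmatic and the evidence preliminary, and leaves more precise estimates to later studies.

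All of this limits the size of the point. None of it answers the core. The limitations paragraph mentions local data, purposive recruitment and generalisability, but not a margin larger than the assumed prevalence. The sampling section still gives prevalence estimation as a purpose of the sample.

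**Conclusion.** The point holds in a limited form. As written, the only stated precision basis for the sample is wrong in its label, and its margin is 2.2 times the quantity to be estimated. It relies on a normal approximation with 0.79 expected positives. The resulting minimum does not justify the sample for the pooled primary proportion, and nothing in the protocol states what 102 provides.

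If P = 0.023 applies to the primary outcome, which the protocol does not establish, 102 children yield about 2.3 expected positives and a 9% chance of none. The binomial figures also treat the children as independent with a common probability. This is a fault in the justification and in how the result will be understood. It does not show that 102 is unusable or that the planned analysis is invalid.

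**What to change.** 1. **Relabel d** as the margin of error (95% half-width).
2. **Replace the justification** with the precision of the fixed sample. For example: the sample is fixed at 102 on practical grounds; if the proportion with a full mutation or premutation is 2.3%, about 2.3 positives are expected and the chance of none is 9%; exact 95% intervals would be 0 to 3.6% for 0/102, 0.2% to 6.9% for 2/102 and 0.6% to 8.4% for 3/102. State whether the 2.3% includes premutations. If that is not known, show a range of values as in the sensitivity table.
3. **Name the interval** for the primary proportion: exact (Clopper-Pearson) or Wilson. A Wald interval would give negative lower limits at 1 to 3 positives and zero width at 0.
4. **Say in advance how an empty result is reported:** 0/102 is an upper 95% confidence limit of 3.6% (from the two-sided exact interval) for this purposively sampled clinic cohort, not evidence that Fragile X is absent.

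The cost is a rewritten sample size paragraph and a line or two in the analysis section, with no added participants. The stated precision will look less favourable. The change should be made before the analysis, for which results are expected by May 2027.

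### The finite population correction that cuts 34.5 to a minimum of 15.7 does not apply, so 15.7 cannot support 17 per zone; the pooled 102 still meets the 5-point margin under simple random sampling

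*Protocol article*

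**What the plan says.** The section Sample size and allocation uses the single-proportion precision formula with Z = 1.96, "P = 0.023 [11], q = 1-P = 0.977" and "d = standard error (5%, 0.05", and obtains 34.5. It then applies a finite population correction. The population size N is taken from the coordinating hospital: "from the records, 12 cases of autism are seen every 5 months in NAUTH, Nnewi, Anambra State. This amounts to 28.9 patients every year". The result is "15.7 (minimum sample size", followed by the allocation: "For the purpose of this study, 17 participants will be selected per geo-political zone, yielding 102 study participants". The section explains that "the sample size was estimated using patient records from the coordinating centre" and concedes that regional variation may not be fully captured.

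The section Sampling technique repeats the allocation ("Equal allocation of participants was adopted, with 17 children per zone, resulting in a total of 102 participants"), gives regional variability as one reason for it, and calls the sample pragmatic.

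The Specific objectives set the target as Nigerian children aged 1 to 18 with any of three diagnoses: intellectual disability, autism or global developmental delay. The Eligibility criteria admit all three. The Abstract and the Outcomes section define the primary outcome as a proportion in the whole cohort, not by zone.

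**The concern.** A finite population correction is valid when the inference is confined to the N units on the list being sampled. The N used here differs from the target in four ways:

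- It counts one hospital, while the target is national and sampled through six hospitals.
- It counts autism only, while two further diagnoses are eligible.
- It covers 12 months, an arbitrary period. Recruitment is planned for February to September 2026, about 8 months.
- The minimum it produces underlies the allocation in all six zones, although no caseload is given for the other five.

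The Discussion weighs how far the findings generalise to the wider Nigerian population, so the inference is not to a closed list of about 29 patients. The target is very large relative to the sample, and the correction should be negligible. Here it more than halves the requirement.

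This is the only sample size justification in the article. A reader could take each zone of 17 as adequately sized for a 5-point margin, and could read a zone with no positives as informative.

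**Working it through.** **Inputs**, all from Sample size and allocation: Z = 1.96, P = 0.023, q = 0.977, d = 0.05, N = 28.9, 17 per zone, 102 in total. The plan labels d a standard error, but the formula uses it as the 95% half-width.

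**1. The plan's own figures.**
- n = Z²Pq/d² = 3.8416 × 0.022471 / 0.0025 = 34.53 (stated 34.5).
- nc = n/(1 + n/N) = 34.5/(1 + 34.5/28.9) = 15.73 (stated 15.7).

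Both reproduce. (12 cases in 5 months is 12/5 × 12 = 28.8 a year rather than 28.9; with 28.8 the result is still 15.7.) The arithmetic is sound; the fault is in applying the correction.

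**2. What 17 children deliver.** The half-width is 1.96 × √(Pq/n).
- Without the correction: 1.96 × √(0.022471/17) = 0.0713, or ±7.1 points.
- With the factor √((N − n)/(N − 1)) = √(11.9/27.9) = 0.653: 0.0713 × 0.653 = 0.0465, or ±4.7 points.

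So 17 reaches 5 points only if the whole population of interest is those 28.9 patients.

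**3. What the formula needs without the correction.** 34.53 rounds up to 35 (half-width 4.97 points). Applied to each zone, that would be 6 × 35 = 210.

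**4. One zone of 17 at P = 0.023.**
- Expected positives: 17 × 0.023 = 0.39.
- Chance of none: 0.977^17 = 0.673. Over six zones, 6 × 0.673 = 4.0 would be expected to show none.
- Exact (Clopper-Pearson) 95% upper limit for 0/17: 1 − 0.025^(1/17) = 19.5%. For 1/17 the exact interval is 0.1% to 28.7%.

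**5. The pooled cohort of 102.**
- Half-width under simple random sampling: 1.96 × √(0.022471/102) = 0.0291, or ±2.9 points.
- Expected positives: 102 × 0.023 = 2.35. The normal-approximation interval around 2.3% would have a negative lower limit (2.3 − 2.9 = −0.6), so an exact interval is the better description: for 2/102 it is 0.2% to 6.9%.
- Clustering by site: the documents give no design effect. Assuming 1.5, 2 or 3, the half-width becomes 3.6, 4.1 or 5.0 points. The 5-point margin is lost once the design effect passes about 102/34.53 = 2.95.

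**The case against.** The strongest reply is that the primary outcome is pooled. For that estimate 102 is about three times the uncorrected 34.5, so removing the correction leaves the 5-point margin met. This stands. A reader might infer from the faulty step that the study as a whole misses its margin; the documents do not support that, short of a design effect near 3.

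A second reply is that no zone-level precision is promised. This also stands. The article gives d = 0.05 without attaching it to zones, and the Statistical analysis plan section names no zone-specific prevalence and no comparison of zones. A reader might infer that a stated zone margin is broken, but such a margin is only implied by setting 17 per zone just above 15.7. Likewise, citing regional variability as a reason for equal allocation can mean no more than that every zone is sampled.

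A third reply is that the limits are already disclosed: the sample is called pragmatic, the local records are offered as the best to hand, and the Discussion lists the sample size basis and purposive recruitment as limitations. This helps less. An uncertain input can be excused that way, but none of this wording says that the correction is inapplicable or that it more than halves the requirement. The derivation also fails on either reading: for a pooled target the formula gives 35, and neither 15.7 nor 6 × 17 follows from it; for a zone target, 17 is about half of what is needed.

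Finally, a 5-point margin is more than twice the assumed prevalence of 2.3%, so meeting it says little. That is fair, and is a further reason to report the interval that 102 delivers rather than rely on d = 0.05.

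**Conclusion.** The concern holds in a limited form. The correction rests on a population that is not the study's target, so 15.7 is not a valid minimum and cannot support 17 per zone. Without it, the plan's formula needs 35 for ±5 points. The pooled 102 meets this at about ±2.9 points; a single zone of 17 does not, at about ±7.1 points.

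The figures assume the plan's P = 0.023. The pooled result also assumes simple random sampling, which purposive recruitment at six sites does not provide, so the stated precision is at best nominal. What needs correcting is the stated justification and the zone-level precision that it implies; the primary estimate keeps its nominal margin.

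**What to change.** In Sample size and allocation, delete the finite population step and the 15.7. State that 102 is a pragmatic total sized for the pooled estimate. Give its expected precision as an exact interval, for example 2/102: about 0.2% to 6.9%, and note that this ignores clustering by site and purposive sampling. In Sampling technique, state that equal allocation serves to spread recruitment over the zones and that zone-level proportions are descriptive only.

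The cost is wording in two sections, with no added patients. The downside is a less favourable justification: the article would no longer show a calculated minimum behind the 17 per zone. If the sponsor wants zone-level precision instead, it must state and justify a margin per zone; at the present ±5 points that means 35 per zone, 210 in all.
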